#### **Safety Population**

The Safety Population is defined as all subjects in the ITT and for whom there is at least one value for safety data.

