### **Analysis Populations**

#### **Intent-to-Treat (ITT) Population**

The ITT Population is defined as all subjects who were enrolled into the study, received treatment and have at least one post baseline value for efficacy data.

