### **9.1.2 Treatment Period**

#### **9.1.2.1 Day 0**

- On day 0 the subject will receive treatment with Rhenium-SCT for their lesion(s). Any AEs are recorded, as well as relevant concomitant medications.
- Urine pregnancy test (females of child-bearing potential)

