#### **9.1.2.2 Day 14**

14 days after the subject receives treatment, they are to enter questionnaire responses of their treatment into the subject trial App. For subjects who don't have a smart phone, this is recorded in the eCRF at the visit using a short questionnaire (see Appendix 4).

Photography is conducted at the site and images loaded to the eCRF. If a medical photographer is available this is favoured, however the site can use an available digital camera.

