## **11.4 Data Sets to be Analysed**

### **11.4.1 Safety Analysis Set**

The safety analysis set comprises all subjects who have received treatment and for whom at least one item of safety data is available. Documentation that the subject did not experience any adverse events constitutes safety information.

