#### **Intent to Treat Set**

The intent to treat (ITT) set comprises all subjects in the FAS who received treatment and for whom at least one item of efficacy data is available.

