### **Secondary efficacy endpoints: Change from baseline in QoL, comfort of treatment, and cosmetic outcomes**

The QoL questionnaire will be scored according to the author's instructions. Change from baseline in score will be calculated. Descriptive statistics will be presented for actual score and change from baseline by timepoint, overall and by tumour type (BCC/SCC). A mixed model will be fitted with change from baseline as the outcome variable. Baseline score will be included as a covariate and timepoint (6 months/12 months) tumour type, tumour stage as factors. Other relevant prognostic factors assessed at baseline will be included. Subject will be included as a repeated term to acknowledge the data structure. From the model the adjusted mean change at each timepoint will be obtained and presented with 95% confidence limits. Adjusted mean change will be estimated overall and by tumour type.

Comfort with treatment is being assessed using a short questionnaire. The frequency (and percentage) of subjects reporting each option for each question will be presented.

Cosmetic outcome (subject and clinician) is being assessed at two timepoints (12 months and 24 months respectively) using a Visual Analogue Scale (VAS). Descriptive statistics will be presented overall and by tumour type (BCC or SCC). A mixed model will be fitted with VAS as the outcome variable. Tumour type and tumour stage will be included as factors. Other relevant prognostic factors assessed at Baseline will be included. From the model the adjusted mean score will be obtained and presented with 95% confidence limits. Adjusted mean score will be estimated overall and by tumour type.

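### The synopsis makes the Safety Population depend on a post-baseline efficacy value and section 11.4.1 does not, so the set used for the adverse event tables is defined in two conflicting ways

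*Protocol*

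**What the plan says.** The synopsis, under Analysis Populations, builds the safety set in two steps. Its ITT Population consists of enrolled subjects who "received treatment and have at least one post baseline value for efficacy data". Its Safety Population is then nested in that set: "The Safety Population is defined as all subjects in the ITT and for whom there is at least one value for safety data".

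Section 11.4.1 defines the same set without reference to the ITT: "The safety analysis set comprises all subjects who have received treatment and for whom at least one item of safety data is available". It adds that "Documentation that the subject did not experience any adverse events constitutes safety information", so a treated subject with a documented absence of events also qualifies.

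Section 11.8.1.1, which describes the adverse event summaries, does not say which set they use. No section of the protocol says that section 11 overrides the synopsis or the reverse.

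**The concern.** Adverse events by severity and by relationship to Rhenium-SCT are the safety endpoint of this post-marketing study. The rates depend on who is in the denominator, and the protocol fixes that in two different ways.

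The synopsis version is the problematic one. It admits a treated subject to the safety tables only once that subject has supplied an efficacy value. A subject with a recorded event but no efficacy value leaves both the numerator and the denominator. Section 7.3.1 lists a treatment-related serious adverse event as a possible reason for withdrawal, so such a subject is foreseeable. If early leavers have more toxicity than those who stay, the reported rates are too low.

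**Working it through.** The protocol gives no size for the safety set and no expected adverse event rate, so there is no planned figure to reproduce. The check compares the definitions, then the timing, then shows an illustration on stated assumptions.

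**1. The definitions side by side**

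- Synopsis: treated AND at least one post-baseline efficacy value AND at least one safety value.
- Section 11.4.1: treated AND at least one item of safety data.

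The synopsis set is contained in the section 11.4.1 set. The difference between them is the treated subjects who have safety data but no post-baseline efficacy value.

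**2. Whether that difference can be non-empty**

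- Safety data start on Day 0. Section 9.1.2.1 says: "Any AEs are recorded, as well as relevant concomitant medications".
- The earliest post-treatment item that could count as efficacy is the comfort questionnaire. Section 9.1.2.2 says: "14 days after the subject receives treatment, they are to enter questionnaire responses of their treatment into the subject trial App". Section 11.7 classes comfort as efficacy: "Secondary efficacy endpoints: Change from baseline in QoL, comfort of treatment, and cosmetic outcomes".
- The first post-baseline response and quality of life assessments are at 6 months (Table 2 and section 9.1.3).
- For a subject who leaves early, section 9.1.4 asks the investigator only to try to arrange a final visit. Section 7.3.1 rules out recording data obtained after consent is withdrawn.

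A treated subject can therefore have adverse event data and no efficacy value. The window is about 14 days if the comfort questionnaire counts, and up to 6 months if only response or quality of life counts. The longer window would cover the whole 30-day period in which all adverse events are collected. The population definitions do not say which items satisfy the efficacy condition.

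**3. Illustration (every rate here is assumed)**

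Let *d* be the share of treated subjects with no efficacy value, *l* their severe-event rate, and *s* the rate in everyone else. Then

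- section 11.4.1 set: R = (1 − d)·s + d·l
- synopsis set: R = s
- shortfall: d·(l − s)

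Take s = 5%.

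| d | l | Section 11.4.1 set | Synopsis set |
|---|---|---|---|
| 2% | 5% | 0.98 × 0.05 + 0.02 × 0.05 = 5.0% | 5.0% |
| 2% | 30% | 0.98 × 0.05 + 0.02 × 0.30 = 5.5% | 5.0% |
| 2% | 50% | 0.98 × 0.05 + 0.02 × 0.50 = 5.9% | 5.0% |
| 10% | 5% | 0.90 × 0.05 + 0.10 × 0.05 = 5.0% | 5.0% |
| 10% | 30% | 0.90 × 0.05 + 0.10 × 0.30 = 7.5% | 5.0% |
| 10% | 50% | 0.90 × 0.05 + 0.10 × 0.50 = 9.5% | 5.0% |

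The rates depend on *d*, not on the number treated. For the count of subjects affected, the protocol offers 120 (minimum analysed), 25 × 7 = 175 (required per site, all sites) and about 210 (recruited). The last allows for screening failures, so it is an upper bound on the number treated. The count then runs from 0.02 × 120 = 2.4, about 2, to 0.10 × 210 = 21.

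Where l = s the rate is unbiased but events still disappear: at d = 10% of 210, 21 × 0.05 = about 1 event.

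**The case against.** A reader might infer that subjects who leave early will drop out of the safety results, taking deaths and serious events with them, and that adverse event rates will be too low. The documents do not support that.

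- The exclusion arises only if the synopsis wording is the one applied. Section 11.4.1, in the statistical section, keeps these subjects, and the statistical analysis plan, which is not shown, may settle the matter.
- Only subjects with no efficacy value at all are affected. Because the protocol itself classes comfort as efficacy and collects it within 14 days, by App for smartphone users (section 9.2.2), someone who answers and then leaves with toxicity stays in the set. On that reading much of the 30-day collection period is not exposed.
- A final examination of withdrawn subjects is requested where possible and could supply an efficacy value.
- Serious events and deaths are documented and reported individually under sections 10.6 and 10.8 whatever the analysis set. They could be missing from tables, not from oversight.
- Downward bias needs *l* to exceed *s*. The protocol does not say that it does.
- The ITT set in section 11.4.2 asks only that a subject be someone "for whom at least one item of efficacy data is available", without requiring that it be post-baseline. If the synopsis Safety Population were read against that ITT, a baseline quality of life score might suffice and hardly anyone would be lost.

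These points limit the size of the effect and make it conditional. They do not remove the conflict. The synopsis Safety Population follows directly on the synopsis ITT, which does require a post-baseline value. The last point adds a further discrepancy between the two sections and does not resolve this one. Nor is the choice of set simply left to a later plan, since the protocol fixes it twice.

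**Conclusion.** The point holds as a contradiction between two current definitions of the safety set, one of which wrongly ties safety reporting to efficacy follow-up. If the synopsis definition is used, treated subjects with adverse event data but no efficacy value are left out of the adverse event tables. Their events are lost, and the rates are biased downwards if they have more toxicity than the rest.

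The size cannot be taken from the protocol. Assuming 2% to 10% of treated subjects have no efficacy value, a 5% severe-event rate in the rest, and 5% to 50% in those lost, the shortfall runs from nothing to 4.5 percentage points (9.5% against 5.0%). The top of that range comes entirely from the assumed rates.

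The primary endpoint and the sample size are not affected. The text still needs correcting, because a stated rule for the safety endpoint is wrong as written and putting it right costs almost nothing.

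**What to change.** In the synopsis, delete the ITT condition from the Safety Population and repeat the section 11.4.1 definition: every treated subject with one or more items of safety data, with a documented absence of adverse events counting as such an item. Section 11.4.1 can stay as it is. There is no need for a third definition that also drops its safety-data condition.

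The result is one safety set, independent of efficacy follow-up, used throughout. The cost is a short edit to the synopsis at the next amendment, with no added data, visits or subjects.

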#### **Efficacy analysis:**

Primary efficacy endpoint: Complete Response (CR).

The number of lesions treated per subject will be summarised.

The number (and percentage) of lesions in each category (CR, PR, SD and progressive PD) at each timepoint (6 months, 12 months and 24 months) and the overall best response will be presented. The percentage of lesions achieving CR during the study (i.e., CR being the best overall response) will be estimated and presented with exact 95% confidence limits overall and by tumour type.

Secondary efficacy endpoints: Change from baseline in QoL, comfort of treatment, and cosmetic outcomes.

The QoL questionnaire will be scored according to the author's instructions. Change from baseline in score will be calculated. Descriptive statistics will be presented for actual score and change from baseline by timepoint, and overall and by tumour type (BCC/SCC). A mixed model will be fitted with change from baseline as the outcome variable. Baseline score will be included as a covariate and timepoint (6 months/12 months) tumour type, tumour stage as factors. Other relevant prognostic factors assessed at baseline will be included. From the model the adjusted mean change at each timepoint will be obtained and presented with 95% confidence limits. Adjusted mean change will be estimated overall and by tumour type.

Comfort with treatment is being assessed using a questionnaire. The frequency (and percentage) of subjects reporting each option for each question will be presented.

Cosmetic outcome (subject and clinician rated) is being assessed at 12 months and 24 months using a visual analogue score (VAS). Descriptive statistics will be presented overall and by tumour type (BCC or SCC). A mixed model will be fitted with VAS as the outcome variable. Tumour type and tumour stage will be included as factors. Other relevant prognostic factors assessed at baseline will be included. From the model the adjusted mean score will be obtained and presented with 95% confidence limits. Adjusted mean score will be estimated overall and by tumour type.

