**Primary endpoint:**

- The number and percentage of lesions achieving CR during the study

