### 7.1 Inclusion Criteria

Subjects meeting the following criteria will be considered for inclusion into the study:

1. Stage I or II BCC or SCC (SCC Well to Moderately Differentiated), and clinically node negative disease
2. Confirmed Histology, and with depth of lesion noted
3. Subjects with up to 3 lesions suitable to enter the study (subjects with more than 3 lesions are not excluded from the study, however 3 target lesions are determined for study evaluation only.)
4. Subjects able and willing to comply with the requirements of the study
5. Age  $\geq 18$  years
6. Informed Consent signed by the subject consenting to undergo the study
7. Lesions up to 8cm^2
8. Lesions with a depth up to 3mm confirmed on biopsy report AND deemed appropriate clinically by treating clinician
9. Subjects who are not deemed suitable for surgery, for example due to tumour location, performance status or other comorbidities as deemed relevant by the treating clinician
10. Patients who may have declined Surgery and/or fractionated Radiation Therapy

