## 11. STATISTICAL METHODS

### 11.1 Determination of Sample Size

The primary objective of the study is to estimate CR rate and show non-inferiority to historical values for CR rate following surgery and or radiotherapy. Complete response rate for BCC is 91% at 5 years and for SCC 79%. Review of the published papers for brachytherapy shows the split between BCC and SCC is 2:1, 1.68:1 and 2.1:1.

Based on previous studies, the CR rate for BCC and SCC is expected to be close to 100% following Rhenium-188 SCT treatment. For simplicity, assuming 1 lesion per subject, a sample size of 120 subjects is sufficient to provide at least 80% power to conclude non-inferiority using a one-sided alpha of 0.025 under the following circumstances (Table 3).

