**Table 3. Sample size calculation**

| Non-inferiority margin | Assumed CR rate |
|------------------------|-----------------|
| 85%                    | ≥94%            |
| 86%                    | ≥94%            |
| 87%                    | ≥95%            |
| 88%                    | ≥96%            |
| 89%                    | ≥97%            |
| 90%                    | ≥97%            |

CR: complete response

Note. A series of simulations (1000) were run to explore the potential impact of different ratios of BCC:SCC on the estimated overall, historical CR rate, assuming the SCC rate was 79% and the BCC rate 91%.

For ratios between 1.5:1 (BCC: SCC) to 3.5:1, the range of median (from simulation) overall CR rate was 87% to 89%. Accordingly, the table above is applicable irrespective of the BCC:SCC ratio.

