## **11.7 Efficacy Analyses**

### **Primary efficacy endpoint: Complete Remission (CR)**

The number of lesions treated per subject will be summarised.

The number (and percentage) of lesions in each category (CR, partial response [PR], stable disease [SD] and progressive disease [PD]) at each timepoint, and the overall best response will be presented. The percentage of lesions achieving CR during the study (i.e., CR is the

best overall response) will be estimated and presented with exact 95% confidence limits overall and by tumour type.

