#### Baseline documentation of Target lesions

- All measurable lesions up to a maximum of three lesions should be identified as **target lesions** and recorded and measured at baseline.
- Target lesions should be selected on the basis of their size (lesions with the longest diameter) and their suitability for accurate repeated measurements (either by imaging techniques or clinically). In addition, the lesions and subject should meet the inclusion criteria.
- A sum of the longest diameter (LD) for *all target lesions* will be calculated and reported as the baseline sum LD. The baseline sum LD will be used as reference by which to characterize the objective tumour.

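### The exact 95% limits on the percentage of lesions in CR treat lesions of one subject as independent; if several lesions per subject are common and correlated, the interval is too narrow and the one-sided error exceeds 2.5%

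*Protocol*

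**What the plan says.** - Unit: the synopsis defines the primary endpoint as "The number and percentage of lesions achieving CR during the study"; section 5.2 says the same.
- Interval: under Efficacy analysis in the synopsis, the percentage of lesions with CR as best overall response "will be estimated and presented with exact 95% confidence limits overall and by tumour type". Section 11.7 repeats this: "best overall response) will be estimated and presented with exact 95% confidence limits overall and by tumour type". Neither place makes any allowance for lesions that belong to the same subject.
- Lesions per subject: Appendix 5 states that "All measurable lesions up to a maximum of three lesions should be identified as" target lesions. Inclusion criterion 3 (section 7.1) admits subjects with more than three lesions, of which "3 target lesions are determined for study evaluation only".
- Sample size: section 11.1 states "For simplicity, assuming 1 lesion per subject, a sample size of 120 subjects is sufficient to provide at least 80% power". The purpose given there is "to conclude non-inferiority using a one-sided alpha of 0.025 under the following circumstances"; they are listed in Table 3, which pairs bounds of 85% to 90% with assumed CR rates of 94% to 97%.
- Section 11.7 has the number of lesions per subject summarised, but that number plays no part in the primary interval.

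**The concern.** An exact binomial interval takes its width from the number of independent observations. Lesions of one subject share skin and immune status, are treated on the same day, and are assessed by the same unblinded site investigator, so some positive correlation is the reasonable expectation. Where it exists, 186 lesions from 120 subjects carry less information than 186 independent lesions, and limits computed on 186 are too tight.

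This interval is the only primary inference that the protocol specifies, and section 11.1 gives showing non-inferiority as part of the primary objective. If the lower limit carries that conclusion, limits that are too tight raise the chance of declaring non-inferiority wrongly. Nor is this a detail left to the SAP: the protocol fixes the method in two places, and an SAP that follows it will carry it over.

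**Working it through.** **1. The plan's own figure.** For an exact one-sample binomial test with n = 120, take the smallest number of responders that keeps the one-sided error at or below 0.025.

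| Bound / assumed CR | Responders needed | Exact one-sided error | Power |
|---|---|---|---|
| 85% / 94% | 110 | 2.2% | 89.3% |
| 86% / 94% | 111 | 2.1% | 81.6% |
| 87% / 95% | 112 | 2.0% | 85.3% |
| 88% / 96% | 113 | 1.9% | 89.1% |
| 89% / 97% | 114 | 1.8% | 93.0% |
| 90% / 97% | 115 | 1.6% | 84.7% |

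Table 3 reproduces. With one lesion per subject the exact method keeps the error below 2.5%, with a little to spare.

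**2. Assumptions for several lesions.** The documents give no lesion distribution for this trial and no ICC. The one related figure is the earlier trial in section 4.3: 55 lesions in 52 patients, 55/52 = 1.06 each. I take three mixes of subjects with 1/2/3 lesions: 94/6/0% (mean 1.06), 60/25/15% (mean 1.55) and 40/30/30% (mean 1.9). ICC runs from 0 to 0.5. The true CR rate equals the bound, at 87% or 88%, inside Table 3 and within the range the protocol derives for the historical rate.

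**3. Design effect and effective sample size.** Design effect = 1 + (E[m²]/E[m] − 1) × ICC, where m is lesions per subject. Effective sample size = 120 × E[m] / design effect.

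- Mean 1.06: E[m²] = 0.94 + 0.24 = 1.18, and 1.18/1.06 − 1 = 0.113. At ICC 0.1/0.3/0.5 the design effect is 1.01/1.03/1.06 and the effective size 126/123/120.
- Mean 1.55: E[m²] = 0.60 + 1.00 + 1.35 = 2.95, and 2.95/1.55 − 1 = 0.903. Design effect 1.09/1.27/1.45; effective size 171/146/128, against 186 lesions counted.
- Mean 1.9: E[m²] = 0.40 + 1.20 + 2.70 = 4.30, and 4.30/1.9 − 1 = 1.263. Design effect 1.13/1.38/1.63; effective size 202/165/140, against 228 counted.

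**4. One-sided error of the unadjusted exact limits.** Beta-binomial simulation, 120 subjects. Non-inferiority is concluded when the lower 95% limit over all lesions exceeds the bound. Simulation error is about 0.1 point.

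| Mean lesions | ICC 0 | ICC 0.1 | ICC 0.3 | ICC 0.5 | Coverage at ICC 0.5 |
|---|---|---|---|---|---|
| 1.06 | 1.6% | 1.7% | 1.8% | 1.9–2.0% | 96% |
| 1.55 | 1.9% | 2.3% | 3.2% | 4.2% | 91% |
| 1.9 | 2.0% | 2.5–2.6% | 3.9% | 5.3% | 89% |

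**5. Effect on a single result.** 171 of 186 lesions in CR (91.9%) gives an unadjusted lower limit of 87.05%, just above an 87% bound. On the effective sample size at design effect 1.27 it is 86.3%, below it. Likewise 222 of 240 (92.5%, mean 2 lesions) gives 88.4% unadjusted, and 87.5% at ICC 0.3 with one third of subjects having each lesion count (design effect 1.40). Both examples lie close to the bound by choice: 170 of 186 (86.4%) fails 87% without any adjustment.

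**6. Does a clustered interval repair it?** I computed exact limits on the effective sample size, with the design effect estimated from between-subject variance and floored at 1. The one-sided error at the 88% bound is then 1.8% to 2.4% for means of 1.3 to 3 lesions and ICC 0.1 to 0.5.

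**The case against.** The strongest reply is that the harm may never arise. The only lesion count per patient in the document is 1.06, and at that level the conservatism of the exact method absorbs the correlation at every ICC up to 0.5. With a mean of 1.55 and ICC 0.1 the error is still below 2.5%. ICC values of 0.3 to 0.5 have no source in the protocol, and section 8.1.1 sets treatment time lesion by lesion, which argues for a lower correlation. All of this stands, and it makes the effect conditional. It does not remove it: the protocol does not limit subjects to one lesion, and Appendix 5 makes every measurable lesion up to three a target.

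The unit is also not uniform. The synopsis (criteria for evaluation) and section 9.2.1 speak of the CR rate for subjects, and Appendix 5 defines CR as the disappearance of all target lesions. The endpoint and section 11.7 nevertheless count lesions, and the interval is placed there.

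Three stronger readings are tempting but unsupported:

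- **The sample size is inadequate because it assumes one lesion per subject.** It is not. Section 11.1 already states 120 as subjects. In every case run (ICC up to 0.5) the effective size was at least 120, and power for 96% against 88% was about 88% or more.
- **The authors recognised lesion clustering for QoL but forgot it for CR.** The repeated subject term in section 11.7 handles the 6- and 12-month visits of one subject, not several lesions.
- **The protocol states that non-inferiority is decided on this lower limit.** It does not. Section 11.7 only estimates and presents the interval; the rule is inferred from the one-sided alpha of 0.025.

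**Conclusion.** The point holds in conditional form. The protocol fixes an interval that assumes independent lesions while allowing up to three per subject. If nearly all subjects have one lesion, the consequence is nil. If multiple lesions are common and correlated, the one-sided error rises from below 2.5% to about 3% to 5% (ICC 0.3 to 0.5, mean 1.55 to 1.9 lesions), and coverage of the nominal 95% interval falls to about 89% at worst in that range. A reader might infer that the interval is always too narrow by a material amount; the figures do not support that.

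These sizes rest on assumed lesion mixes and ICCs, on 120 analysed subjects, and on reading non-inferiority from the lower 95% limit. The flaw should be fixed before the primary data are analysed, but it does not undermine the design or the recruitment target.

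**What to change.** In section 11.7 and the synopsis:

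- Keep the percentage of lesions in CR as the estimate, but give it subject-clustered 95% limits, overall and by tumour type. One workable choice is exact limits on the effective sample size, with the design effect estimated from the data and floored at 1.
- Name a fallback for few or no failures, since the protocol expects a CR rate close to 100% and a design effect cannot be estimated without failures. Options are exact limits with the number of subjects as the effective sample size, or the subject-level rate. With no failures among 120 subjects the first gives a lower limit of 0.025^(1/120) = 97.0%, above every bound in Table 3. It is conservative while ICC is below (E[m] − 1)/(E[m²]/E[m] − 1), which is 0.53, 0.61 and 0.71 for the three mixes. Above that, the subject-level rate is the safer choice.
- State that the non-inferiority conclusion uses the lower clustered limit.
- Report the subject-level CR rate (all target lesions in CR) with exact limits as a sensitivity analysis.

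No change to section 11.1 or to recruitment is needed on this ground. The cost is protocol and SAP wording and minor programming. The interval becomes modestly wider if many subjects have several lesions, and hardly changes otherwise.
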